## Abstract

Aging is associated with an increased risk of developing cardiovascular disease which is often accompanied by a decline in vascular health and function. Current evidence suggests that berries may have a potential role in the modulation of vascular function, but dietary interventions are still needed to confirm findings, especially in older subjects. In the context of the MIND FoodS HUB project, this study aims to investigate the effect of a single serving of blueberry (250 g of blueberry versus a control product) in a group of older subjects (≥ 60*y*) through a randomized, controlled, cross-over dietary intervention trial. Specifically, the study evaluates the absorption kinetics of bioactives following the blueberries intake and the effects on markers related to oxidative stress, inflammation, and vascular function analyzed at different time points. By considering a drop-out rate estimate of 25%, at least 20 subjects will be recruited in the study. The study will provide evidence to support the potential beneficial effects of blueberry and its bioactive compounds on vascular function in a group of population more susceptible to vascular dysfunction and to the development of cardiovascular diseases. Moreover, the study will contribute the analysis of several metabolic and functional markers that can support the biological plausibility of the results obtained. Finally, the trial will provide data on the absorption and metabolism of blueberry bioactives which will be used to study their association with the different markers under study.

**Trail registration:** The trial is registered at ISRCTN (http://isrctn.com/ISRCTN18262533); May 7, 2021.

## Introduction

Aging is a complex and progressive phenomenon characterized by a decrease in functionality of numerous physiological processes at both molecular, cellular, tissue, and organ level, leading to an increased risk of oxidative stress, inflammation and, in turn, development of certain chronic degenerative diseases [1–5]. According to the Global Burden of Disease Study 2019, cardiovascular diseases (CVDs) still represent the leading cause of death in the world, particularly in older subjects [6]. The increased risk of developing CVDs during aging is mainly due to modifications to arteries and the establishment of vascular endothelial dysfunction [7]. The senescent process in endothelial cells leads to an alteration of arterial structure and functionality by reducing the production of vasodilators, such as nitric oxide (NO), and shifting toward the production of vasoconstrictors, procoagulants, proliferative and pro-inflammatory intermediates [8]. These factors are considered as critical for the development of endothelial dysfunction, arterial stiffness and vascular diseases [8–10].

Diet and dietary factors play a crucial role in maintaining normal physiological functions and promoting health. Among dietary factors, (poly)phenols, including flavonoids and phenolic acids, have been identified as potential bioactives able to improve CV health [11]. Recent observational studies report an overall inverse association between (poly)phenol intake and CV risk events and mortality [12–15]. In addition, mechanistic and human intervention studies seem to support the potential role of polyphenols in the modulation of several biomarkers related to vascular/endothelial function and CVDs [16–19]. Blueberries are one of the foods richest foods in (poly)phenols, particularly anthocyanins (ACNs), which are, among the (poly)phenols sub-classes, those mostly associated with CV health [19, 20]. In addition, blueberries are a source of minerals, vitamins, fiber, and salicylates [21] that could contribute, alone or synergistically, to the overall beneficial effect on vascular function [17, 22]. Short and long-term human intervention studies have documented that the consumption of blueberries may improve vascular function, reduce blood pressure and arterial stiffness in healthy subjects but also in those with risks for CVDs, metabolic syndrome, and type 2 diabetes [23–26]. To the best of our knowledge, few and contrasting studies have investigated the contribution of plant-based foods in the promotion of vascular function in older subjects [27] and only one trial tested the effect of blueberries, reporting no effect on markers of arterial stiffness [28]. Based on these premises, providing evidence of the potential health benefits of polyphenol-rich foods on vascular health is relevant in the current demographic context also due to the almost world-wide increase in the number of older people [29].

## Aim

The goal of this study is to evaluate the effect of a single portion of blueberries on markers of vascular function, oxidative stress, and inflammation in older subjects. In addition, the absorption kinetics of blueberries’ bioactive compounds will be assessed and the data obtained correlated with the other biological markers under study.

## Methods/Design

### Protocols and study design

This study follows a randomized, controlled, cross-over design (single portion of blueberry versus a control product) in a sample of free-living older subjects (≥ 60*y*). The study involves two phases (Phase 1 and 2), both including two different appointments, each one spaced by a 1 week wash-out period, as illustrated in the SPIRIT schedule of enrollment, interventions, and assessments (Fig 1 and S1 Checklist).

**Fig 1 pone.0275132.g001:**
[figure not shown]
Schedule of enrollment, interventions, and assessment: Recommendations for interventional trials (SPIRIT).

Phase 1 is aimed at evaluating the absorption of blueberry polyphenols and the effect of blueberries consumption on markers of vascular function (i.e., endothelin-1, NO, ICAM-1, VCAM-1 and VEGF), inflammation (i.e., IL-6, IL-8, and TNF-*α*), oxidative stress (i.e., levels of DNA damage), blood glucose and insulin response (Fig 2). Phase 2 is devoted to the evaluation of vascular functionality, using a non-invasive biosensor and the assessment of reactive hyperemia index (RHI), Framingham reactive hyperemia index (fRHI) and arterial stiffness (i.e., augmentation index (AI) and AI@75); in addition, blood pressure is recorded, as depicted in Fig 3. The approach, divided into two phases, is necessary to facilitate blood drawing (venous cannula) and the evaluation of vascular function (at the level of the brachial artery) avoiding potential sources of interferences between the two measurements. The day before the experiment, participants receive a list of instructions to follow. Following these instructions, subjects are asked to maintain their habitual lifestyle habits (also in terms of physical activities) and to refrain from consuming foods rich in (poly)phenols (e.g., berries, tea, coffee, chocolate, fruit juices). In addition, to limit the possible noise deriving from a long-fasting period the day of the experiment, subjects participating at the Phase 1 are invited to consume a standardized light breakfast. Specifically, volunteers can consume 200 mL of partially skimmed milk or 125 g of yogurt and 3 biscuits (i.e., shortbread) or 3 rusks. The meal has to be consumed at least 90 min before blood collection and at the same hour each test day. The adherence to instructions is evaluated through a food diary and a face-to-face interview that will be scheduled the day of the experiment. In addition, subjects are motivated to complete all the intervention by providing them with free meals the test days and with the access to all laboratory analysis at the end of the trial.

**Fig 2 pone.0275132.g002:**
[figure not shown]
Schematic representation of the study design for the evaluation of blueberry bioactive absorption and of different metabolic/functional markers (phase 1).

**Fig 3 pone.0275132.g003:**
[figure not shown]
Schematic representation of the study design for the evaluation of the effects of intervention on vascular function markers (phase 2).

### Trial status

The trial has been prospectively registered (May 7, 2021; ISRCTN18262533) and is currently ongoing.

### Location

The study is carried out at the Department of Food, Environmental and Nutritional Sciences (DeFENS), Università degli Studi di Milano (Milan, Italy) through its International Center for the Assessment of Nutritional Status (ICANS).

### Participant enrollment

For the study, a group of 20 subjects (age ≥ 60*y*; 10 women and 10 men) are enrolled. The enrollment is carried out through advertisements by using emails, social networks, bulletin boards, and by word of mouth. The subjects who express their willingness to participate undergo a first general medical anamnesis through questions about their health status and their lifestyle (e.g., diseases, use of drugs and supplements, dietary habits, alcohol consumption, and physical activity) followed by an accurate clinical evaluation to confirm their eligibility to participate. Subjects interested in participating in the study sign an informed consent in which they agree with all the information on the dietary intervention, the analysis, and protocols that they are asked to follow. Volunteers are selected according to the inclusion and exclusion criteria reported below:

### Inclusion criteria

Age ≥ 60*y*.

### Exclusion criteria

Diabetes;Major condition related to cardiovascular system (e.g., a medical history of thrombosis or myocardial infarction);Presence of allergies (or other adverse reaction) to the ingestion of blueberry.

Changes in the volunteer status during the experimentation (e.g. occurrence of an exclusion criteria such as drug prescription, not evidenced at the enrolment) will be assessed to define the need of final exclusion from the study.

### Blueberry and control product

Blueberry product consists of a mousse obtained by shredding a serving of blueberries (organic highbush blueberries, cultivar Legacy) able to provide at least 300 mg of anthocyanins (ACNs). This amount of ACNs is considered sufficient to induce an improvement of vascular function as previously reported [30, 31]. The control product consists of a drink prepared by suspending the same amount of fructose, glucose, and saccharose of blueberry (matching the blueberry product for energy) in water, as already published [30, 31].

### Information on potential adverse effects

Even though no reports of adverse effects due to a blueberry consumption have been registered or reported in the literature, subjects are advised to annotate and communicate any adverse symptom perceived during the intervention period.

### Biological sampling

Blood samples (7 mL) are collected at baseline (t0) and after 1 h (t1), 1 h 30 ‘(t2), 2 h (t3) and 4 h (t4) from the consumption of blueberry or control product, as depicted in Fig 2. A cannula needle is used to facilitate blood collection procedures and minimize the discomfort of the volunteers. Tubes containing silicon for serum and tubes containing heparin as anticoagulants for peripheral blood mononuclear cells (PBMCs) are used. An aliquot of blood (500 μL) is immediately processed to obtain PBMCs, while the rest of the blood is maintained at room temperature (22°C) for 30 min before being processed by centrifugation at 1088 g for 15 min at 4°C. The serum obtained is collected, divided in aliquots, and stored at -80°C until analysis.

### Outcome measurements

The primary selected outcome of the study is RHI as a vascular function marker, while other markers including vascular function (i.e., fRHI, AI, AI@75, Endothelin-1, NO, ICAM-1, VCAM-1 and VEGF), inflammation (i.e., IL-6, IL-8, and TNF-*α*) and oxidative stress markers (DNA damage), together with circulating levels of (poly)phenols, salicylates, glycaemia and insulin, are included as secondary outcomes to support and validate the study hypothesis.

### Anthropometric measurements

Body weight and height are assessed at the beginning of the study by trained personnel following the international guidelines reported by Lohman et al. [32]. BMI calculation is obtained by dividing a person’s weight by the height to the power of 2 (BMI = weight (kg) / height (m)2).

### Blood pressure

Volunteers are monitored during each intervention period measuring both systolic and diastolic blood pressure (SBP and DBP) obtained in a resting, seated position based on the validated JNC 7 guidelines [33].

### Metabolic and functional markers

At enrollment, metabolic and functional parameters (i.e., glucose, insulin, lipid profile, liver, and renal function) are analyzed by a standardized validated protocol, using an automatic biochemical analyzer (YSI 2300 STAT Plus Glucose and Lactate Analyzer, Marshall Scientific, Hampton, VA, USA)). In details, non-high density lipoprotein cholesterol (non-HDL-C) is calculated by subtracting high density lipoprotein cholesterol (HDL-C) from total cholesterol (TC) while low density lipoprotein cholesterol (LDL-C) concentration is estimated using the Friedewald formula [34]. The levels of insulin sensitivity are assessed using the widely used homeostasis model assessment for insulin resistance (HOMA-IR), that is calculated considering fasting plasma concentrations of glucose and insulin, as indicated by Wallace et al. [35]. The blood samples are used for the evaluation of: i) kinetics of the absorption of the anthocyanins by gas chromatography–mass spectrometry analysis (GC–MS); ii) kinetics of the absorption of salicylates by means of ultra-performance liquid chromatography tandem mass spectrometry (UPLC-MS/MS); iii) serum markers of vascular function (i.e. ET-1, NO, ICAM-1, VCAM-1 and VEGF) and inflammation (i.e. IL-6, IL-8, and TNF-*α*) evaluated through ELISA kit, while serum markers of oxidative stress (i.e. levels of DNA damage) evaluated through comet assay iv) blood glucose concentrations evaluated by oxidation with YSI 2300 STAT Plus Glucose and Lactate Analyzer and insulin levels determined by ELISA kit.

### Vascular function and arterial stiffness

Endothelial-dependent vasodilation in the small finger arteries is assessed by a non-invasive plethysmographic method (Endo-PAT 2000, Itamar Medical Ltd, Caesarea, Israel) as described elsewhere [36, 37]. Briefly, the Endo-PAT equipment consists of two finger-mounted probes, which include a system of inflatable latex aircushions. The pulsatile volume changes of the fingertip are sensed by a pressure transducer, located at the end of each probe, and transferred to a personal computer where the signal is transduced, amplified, displayed, and stored. For the evaluation, subjects are requested to lie down in a supine position, with both hands on the same level, in a comfortable and thermoneutral environment. Then, a blood pressure cuff is placed on one upper arm (study arm), while the contralateral arm serves as a control arm. After a 10 min equilibration period, the blood pressure cuff on the study arm is inflated to 200–220 mmHg for 5 min. The cuff is then deflated to induce reactive hyperemia while the signals from both PAT channels (Probe 1 and Probe 2) are recorded by a computer. The RHI, an index of the endothelial-dependent flow-mediated dilation, is derived automatically in an operator independent manner. In fact, RHI is calculated as the ratio of the average pulse wave amplitude during hyperemia (60–120 s of the post-occlusion period) to the average pulse wave amplitude during baseline in the occluded hand, divided by the same values in the control hand and then multiplied by a baseline correction factor. According to manufacturing indications, an RHI value of 1.67 provides a sensitivity of 82% and a specificity of 77% for diagnosing endothelial dysfunction [38].

The Endo-PAT tool also provides the digital augmentation index (AI), a measure of pulse wave reflection and a surrogate marker for arterial stiffness. AI derives from digital pulse volume waveforms and it has been reported to be strongly correlated with aortic AI. Peripheral AI is calculated from the shape of the pulse wave recorded during baseline [39, 40]. Since digital AI is affected in an inverse and linear manner by heart rate (HR) [41], the AI was automatically normalized by considering a HR of 75 bpm (AI@75).

### Vascular and inflammatory markers

The concentrations of several markers related to vascular and inflammatory processes are quantified at least in duplicate using specific ELISA or colorimetric assay kits according to the instructions of each producer (Boster Bio, [name]; Cayman Chemical Company, Ann Arbor, MI, USA). The following kits are used on serum samples obtained at each time points during the intervention periods: IL-6: BSR-EK0410—Human IL-6 PicoKine ELISA Kit, IL-8: BSR-EK0413—Human IL-8 PicoKine ELISA Kit, TNF-*α*: BSR-EK0525—Human TNF alpha PicoKine ELISA Kit, Endothelin-1: BSR-EK0945—Human Endothelin PicoKine ELISA Kit, ICAM-1: BSR-EK0370—Human ICAM-1 PicoKine ELISA Kit, VCAM-1: BSR-EK0537—Human VCAM-1 PicoKine ELISA Kit, VEGF: BSR-EK0539—Human VEGF PicoKine ELISA Kit, NO: CAY-780001–2x96—Nitrate/Nitrite Colorimetric Assay Kit.

### Oxidative stress markers

The levels of oxidatively-induced DNA damage, as markers of oxidative stress, are assessed in PBMCs by the comet assay on an aliquot of fresh blood, immediately after its withdrawal. Oxidatively-induced DNA damage is measured by treating the cells with hydrogen peroxide and by evaluating the capacity of cells to counteract this oxidative insult. This procedure is performed according to Del Bo’ et al., [42]. Briefly, cell resistance against oxidatively induced DNA damage is measured by treating the isolated PBMCs with hydrogen peroxide (H2O2). Two slides with two gels each are prepared for each sample. One slide is treated with H2O2 (500 μmol/L in PBS) for 5 min in the dark, while the other slide is treated with PBS without H2O2, as it is used as a control. Following oxidative treatment, the slides are placed in lysis buffer (2.5M NaCl, 0.1M Na2 EDTA, 10mM Tris, 1% Triton X-100, 1% DMSO, and 1% N-lauroylsarcosine sodium salt, pH 10) for 1h at 4°C in the dark. After lysis, the gels are washed in buffer (40nM HEPES, 0.1M KCl, 0.5mM EDTA and 0.2mg/ml bovine serum albumin, pH 8) and then transferred to electrophoresis buffer (0.3M NaOH and 1mM Na2 EDTA) and incubated for 40min at 4°C in the dark. Electrophoresis is performed at 1.1V/cm2 for 20min. Slides are successively neutralized (0.4M Tris–HCl, pH 7.5) for 15min at 4°C in the dark, stained with ethidium bromide (2 μg/ml), washed in PBS, drained and coverslipped to permit the subsequent quantification of DNA damage through an epifluorescence microscope attached to a high sensitivity CCD video camera and to a computer equipped with an image analysis system (QCapture 2.9.13, Irvine, CA, USA; DNA COMET1.50.00, University of Milan, Italy). The levels of DNA damage are calculated as the percentage of DNA in the tail.

### Serum anthocyanins

Serum samples are used to determine the kinetics of absorption of blueberry ACNs and salicylates. The extraction and analysis of ACNs from serum are performed through a microelution solid phase extraction (SPE) and ultra-HPLC methods, according to Martí et al., [43]. Briefly, prior to injection in the UPLC-MS/MS, ACNs are extracted using μElution Plates 30 mm conditioned with 250 mL of methanol and 250 mL/mL of 0.2%acetic acid. Then 350 μL of plasma is mixed with 350 μL of phosphoric acid 4%, loaded into the plate. The loaded plates are washed with 200 μL of Milli-Q water and 200 μL of 0.2%acetic acid. Then, the retained ACNs are eluted with 2 x 50 μL of acetone/Milli-Q water/acetic acid solution (70:29.5:0.5, v/v/v) and injected. Injection volume is 2.5 μL. UPLC-ESI-MS/MS is constituted by a stationary phase of 100% silica particles, particles while the mobile phase by 10% acetic acid (eluent A) and acetonitrile (eluent B). The flow rate is set at 0.4 mL/min.

### Blood salicylates

The analysis of salicylates in serum samples is performed using stable isotope dilution and gas chromatography–mass spectrometry analysis (GC–MS), as described previously [44]. Briefly, following adjustment for the pH to about 1.0 with hydrochloric acid, the organic material is extracted twice with ethyl ether and ethyl acetate (2 mL), and then is collected for derivatization prior to GC–MS analysis. Analysis is then carried out using a gas chromatograph interfaced with a single-quadrupole mass spectrometer equipped with a chamber provided with an electron ionization source and using helium as carrier gas. Finally, the identification of derivative salicylic acid is achieved by comparing the gas chromatographic retention times and the mass spectra of the serum samples with those of the standards.

### Data management

Data management includes a strict control of data quality and check of accuracy of data entry. To ensure data protection, data will be saved in a password-protected Excel file on an electronic device equipped with an antivirus system locked up in a secure location when not in use. Once completed final data will be stored in an electronic database (Dataverse). Identifiable data are not recorded in the database or other documents, and participants are identified by a unique trial ID only. Hard copies of data sheets linking the participant identification number to the person’s contact details are kept securely within the University premises that are accessible only to dedicated research team members. Participant files and other source data (including copies of protocols, questionnaires, and original reports of test results, correspondence, records of informed consent and other documents pertaining to the conduct of the study) are kept for the maximum period of time permitted by the institution.

### Sample size, randomization, and statistical analysis

The sample size is determined based on previous studies conducted in our laboratories (30–31) and other research groups [26, 28, 45] to test the efficacy of a blueberry consumption on markers of vascular function. Twenty volunteers are enrolled for the study. This number is considered sufficient (alpha = 0.05, 80% power) to determine an increase of 0.30 in the RHI parameter (endothelial function marker) after blueberry intake. This calculation also considers a possible drop out of 25% of the volunteers. Subjects are randomly divided using a computer random number generator. The randomisation and allocation is performed by a person not involved in the trial and blinded to the investigators and researchers involved in samples analysis. The statistical analysis is performed by means of STATISTICA software (Statsoft Inc., Tulsa, OK, US). Only complete data obtained will be analysed. The Shapiro–Wilk test is applied to verify the normal distribution of the variables under study. In particular, the following statistical elaborations are performed to identify significant differences between treatments: (i) the analysis of variance (ANOVA) with repeated measures, (ii) Wilcoxon paired data test, (iii) Linear Mixed Model (LMM) analysis. Furthermore, regression and correlation analyses (Spearman and Kendall test) are carried out to highlight potential associations between vascular activity, and markers of inflammation, vascular function, oxidative stress, other than biochemical and physiological markers. Corrections for potential confounding factors (i.e., age, gender, drugs/medications) are performed. When appropriate, a post-hoc p-value adjustment is performed using the Hochberg-Benjamin correction. Significance is set at p<0.05; significance in the range 0.05 < p < 0.10 is indicated as trend.

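### The complete-data rule discards partial data that the listed linear mixed model could use, and leaves the estimate open to avoidable selection bias

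*Protocol article*

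**What the plan says.** All of the rule stands in the section *Sample size, randomization, and statistical analysis* of the protocol article. It reads "Only complete data obtained will be analysed", with no qualification, no definition of complete and no reason given.

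The same section says "Twenty volunteers are enrolled for the study" and, of the sample size, "This calculation also considers a possible drop out of 25% of the volunteers". The Abstract calls the 25% an estimate: "By considering a drop-out rate estimate of 25%, at least 20 subjects will be recruited in the study". The listed methods are repeated-measures ANOVA, then "ii) Wilcoxon paired data test, (iii) Linear Mixed Model (LMM) analysis".

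On the design, *Protocols and study design* says "The study involves two phases (Phase 1 and 2), both including two different appointments", which makes four visits per volunteer. *Biological sampling* sets five blood draws per product in Phase 1, so ten per person. The Discussion sets vascular measurements at baseline and 2 h for each product in Phase 2, so four recordings per person. *Outcome measurements* makes RHI the primary outcome and the Phase 1 markers secondary.

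Two other statements bear on why data might be lost. The Discussion lists as a limitation that participants are not blind. *Exclusion criteria* allows a change in a volunteer's status during the trial to lead to final exclusion.

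**The concern.** A complete-case analysis is unbiased in general only if the people with complete data are a random subset of those randomised. Here volunteers know what they received, may leave at any time, and may be excluded after enrolment. Loss unrelated to treatment or outcome cannot be taken for granted.

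A likelihood-based mixed model with a random subject effect uses whatever each volunteer supplied and is valid under the weaker missing-at-random assumption. The plan lists that model and then, by the complete-data rule, removes the advantage.

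The rule is also ambiguous. Complete could mean complete for the marker being analysed or complete for the whole trial. On the second reading, a volunteer with both Phase 2 visits intact but a missed Phase 1 visit could drop out of the primary RHI analysis. If the choice is left until the data are seen, it affects who enters that analysis.

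**Working it through.** **1. The plan's own figure.** 15 / (1 - 0.25) = 20, and 20 x 0.75 = 15. Twenty enrolled is consistent with 15 completers, so the planned 80% power already refers to complete cases.

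The article gives no SD for the paired RHI difference, so the 15 cannot be derived independently. Back-solving a two-sided paired t-test (n = 15, effect 0.30, alpha 0.05, power 80%) implies an SD of the difference of about 0.385. This value is an assumption in steps 3 and 4. For SDs from 0.3 to 0.6, power with 15 pairs runs from 95% to 44%.

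**2. How much is discarded.** A drop-out has missed at least one of four visits. Five drop-outs therefore have at most 5 x 3 = 15 completed visits. For RHI, someone who leaves during Phase 2 has at most one usable product visit, so at most five such visits are discarded.

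**3. Precision for RHI.** Assumptions: one value per period; 15 complete pairs; all five drop-outs supply period 1 only, split about evenly between sequences; within-subject correlation rho; treatment and period fixed, subject random. A complete pair carries information 1/[2s²(1 - rho)], where s is the SD of a single value. Five one-period volunteers carry 5/(4s²) between them. The ratio gives

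effective pairs = 15 + 5(1 - rho)/2.

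| rho | effective pairs | approximate power |
|---|---|---|
| complete cases only | 15 | 80% |
| 0.2 | 15 + 2.0 = 17.0 | 85% |
| 0.5 | 15 + 1.25 = 16.25 | 83% |
| 0.8 | 15 + 0.5 = 15.5 | 81% |

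If the drop-outs leave before any RHI visit, the gain is zero.

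**4. Bias for RHI.** Assumptions: true effect 0.30; SD of the difference 0.385, so s = 0.385/√[2(1 - rho)]; 25% drop out after period 1. Let Δ be the mean upward shift in the period-1 value among those who stay, by sequence. The period-adjusted complete-case estimate is then

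0.30 + (1 - rho)(Δ for blueberry-first - Δ for control-first)/2.

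Worked extreme case: all loss is the lower half of period-1 values in the blueberry-first sequence, at rho = 0.5. Then s = 0.385, Δ for blueberry-first = 0.798 x 0.385 = 0.307, Δ for control-first = 0, and the estimate is 0.30 + 0.5 x 0.307/2 = 0.377.

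| Drop-out pattern | rho 0.3 | rho 0.5 | rho 0.7 |
|---|---|---|---|
| Completely at random | 0.30 | 0.30 | 0.30 |
| Lowest 25% of period-1 values | 0.25 | 0.27 | 0.28 |
| Lower half, blueberry-first only (extreme) | 0.39 | 0.38 | 0.36 |

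Simulation gives these values. In every pattern, a likelihood analysis of all available data returns 0.30, because loss depends only on an observed value.

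**5. Sporadic sample loss.** The loss rates and their independence are illustrative assumptions; the article gives none. The expected share of volunteers with a full series is (1 - loss rate) to the power of the number of measurements.

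| Assumed loss | Phase 1 marker, 10 samples | RHI, 4 recordings |
|---|---|---|
| 2% | 0.98^10 = 82% (16 of 20) | 0.98^4 = 92% (18 of 20) |
| 5% | 0.95^10 = 60% (12 of 20) | 0.95^4 = 81% (16 of 20) |

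The 25% allowance is for volunteers who drop out. If 15 remain and 5% of samples are lost, 15 x 0.60 = 9 have a complete Phase 1 series.

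**The case against.** The strongest reply is that the plan has paid for this rule in advance. That stands: a reader might infer that the trial is underpowered because of the rule, but the 20 already includes the 25%, and the recoverable RHI information is at most about two pairs. Nor do all 20 visits of five drop-outs go to waste, since visits never made are lost under any method.

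A second reply is that bias is not shown. That also stands. Intolerance of the cannula or cuff would not by itself be specific to one product, because both are used identically under both, and the cannula belongs to Phase 1. With loss completely at random the bias is zero. The shifts above need loss that follows the period-1 result, and the largest is a deliberately extreme case. The mixed model protects only under missing at random; if leaving depends on unobserved values, it need not remove the bias.

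Third, the rule may simply mean complete values for the marker analysed. The article nowhere says that a missed Phase 1 visit removes a volunteer from the RHI analysis, and the phases are separate days measuring different outcomes. The cross-phase exclusion is one possible reading; what can be held against the text is that it does not rule that reading out.

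None of this supplies a reason to discard partial data. Nor is the point a detail left to an analysis plan that is not shown: the article fixes the rule itself.

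**Conclusion.** The point holds as a should-fix. The rule forgoes the protection that the listed mixed model offers against loss related to observed results, and it leaves the analysis set undefined.

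For RHI, the bias in the scenarios examined is zero with loss completely at random, about -0.02 to -0.05 on a true 0.30 when the lowest quarter leaves, and about +0.06 to +0.09 in the extreme one-sequence case. The precision cost for RHI is small, 0 to about 2 pair-equivalents. For ten-sample Phase 1 markers, all secondary, it can be material even at low rates of sample loss.

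These sizes rest on the back-solved SD of 0.385, the assumed correlations and drop-out patterns, and the illustrative loss rates. The documents do not support reading the 25% as a forecast of loss that must occur: the methods section calls it possible and the Abstract an estimate.

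**What to change.** Replace the complete-data sentence along these lines: *All randomised volunteers with at least one post-consumption value for an outcome are analysed in a linear mixed model with treatment and period as fixed effects and subject as a random effect, using all available observations, with small-sample degrees of freedom where the software allows. Each phase is analysed independently of completion of the other. The analysis assumes that data are missing at random. Complete-pair analyses (repeated-measures ANOVA or paired Wilcoxon test) are sensitivity analyses.*

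Subject must be random: with fixed subject effects, a volunteer with one period only adds nothing to the treatment comparison. The last sentence is needed because the ANOVA and Wilcoxon test use complete series or pairs and are now listed beside the mixed model without a stated role.

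The cost is a few sentences, a little more analysis work and open reliance on missing at random. No new data are needed. As the trial is described as ongoing, the change should be made before outcome data are examined.
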